### Participant timeline

Participant timeline is described in Fig. 2.

**Fig. 2 Fig2:**
[figure not shown]
Schedule of enrolment, interventions and assessments

### Randomization and allocation

Participants will be randomly assigned to the acuTENS or sham acuTENS group with a 1:1 allocation by using a computer-generated randomization list. A blocked randomization list will be generated for each centre by the main author, who will not be involved in recruitment or assessment. Randomization lists will be kept by using an electronic key and will be available only to the persons responsible for administering the treatments.

Once participants give consent for participation, a consecutive number will be assigned by the head of recruitment, and the staff responsible for administrating the treatment will match the patient’s number with the randomization list to define the patient’s allocation.

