## Methods

### Study setting

The study will be performed at the “Hospital del Mar” in Barcelona (Spain) and the “Hospital de Sant Joan de Déu de Manresa” in Manresa (Spain).

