#### Secondary outcome measures

Hospitalization length will be measured by using the number of days from the time of admission until the patient’s discharge. Scores will be compared by using mean differences between groups.

Peak expiratory flow will be assessed by using a peak flow meter and using litre per minute units at baseline and after each treatment session. For each assessment, peak flow will be measured three times and only the highest score will be considered. Differences will be assessed between groups by using mean scores at each day (days 1 to 5).

Adverse events will be recorded after each treatment session; the evaluator will ask the patient for any adverse event related to the intervention. Description of each event and its frequency will be described for each group.

Blood gas analysis—partial pressure of oxygen (PaO_2_), partial pressure of carbon dioxide (PaCO_2_), arterial blood pH, bicarbonate and oxygen saturation (SaO_2_)—at days 1 to 5 will be recorded if available in the patient’s clinical history since no specific analysis will be made for the trial. Differences will be assessed by comparing means at each day (days 1 to 5).

Relapse and readmissions at 3 months after discharge will be assessed by using the participant’s clinical history. Mean number of relapses and readmissions during the 3-month period after discharge will be compared between groups.

Mortality will be assessed by using the ratio of patients who died during the 3-month period after discharge in each group.

Quantity of drugs administered during patient’s hospitalization will be extracted from the patient’s clinical history. Mean dosages will be compared between groups. Data will be collected by using a standard form designed by the study investigators, and database entry will be double-checked.

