### Statistical methods

There will be a descriptive analysis of the demographic data by using means and standard deviations (mean ± standard deviation) for continuous variables and absolute values and percentages for qualitative outcomes.

For the comparative analysis between the two groups, continuous outcomes (such as Borg scale score and number of hospitalization days) will be analysed by using mean differences with a 95% confidence interval with a Student *t* test or Mann–Whitney *U* test depending on the distribution of these. For dichotomous outcomes (such as mortality at 3 months), risk ratio will also be used with a confidence interval of 95% and chi-squared test.

The main analysis will be carried out by intention to treat, but there will be another per-protocol analysis for patients who have received at least three interventions. A *P* value of less than 0.05 will be considered significantly different.

In case of missing data, last value carried forward methods will be used. In case of significant baseline differences between the two groups, there will be an adjusted analysis for these outcomes.

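### Randomisation is stratified by hospital but the fixed analysis ignores hospital, which costs precision if outcomes differ between the two sites

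*Protocol article*

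**What the plan says.** **Design.** The Study setting section names two sites: "The study will be performed at the “Hospital del Mar” in Barcelona (Spain) and the “Hospital de Sant Joan de Déu de Manresa” in Manresa". Under Randomization and allocation, participants are assigned "with a 1:1 allocation by using a computer-generated randomization list", and "A blocked randomization list will be generated for each centre by the main author". Each hospital therefore has its own blocked list, which makes centre a stratification factor. The block size is not given.

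**Analysis.** Under Statistical methods, "continuous outcomes (such as Borg scale score and number of hospitalization days) will be analysed by using mean differences with a 95% confidence interval"; the choice between Student t and Mann–Whitney U is made by distribution. For dichotomous outcomes, "risk ratio will also be used with a confidence interval of 95% and chi-squared test". Under Secondary outcome measures, length of stay is handled in the same way ("Scores will be compared by using mean differences between groups"), as is drug quantity ("Mean dosages will be compared between groups"). None of these comparisons has a centre term or a stratified test.

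**Adjustment.** The one rule is conditional: "In case of significant baseline differences between the two groups, there will be an adjusted analysis for these outcomes". Centre is not named.

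**The concern.** Blocking within each hospital makes the two arms nearly equal in their mix of hospitals. A difference between hospitals then largely cancels out of the treatment comparison, so the true variance of the group difference excludes most of the between-hospital variance. The ordinary two-sample standard error does not know this. It pools all patients in an arm and keeps the between-hospital variance in the error term. If the hospitals differ on an outcome, the reported standard error is too large for the design that produced the data.

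Precision is what is at stake. The trial is small, it is powered on the Borg score alone, and the Discussion hopes for reductions in medication and hospital days, for which the article gives no power calculation. An interval wider than the design requires makes a real effect harder to show.

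**Working it through.** **1. The plan's own figure.** Inputs from Sample size: difference 2, SD 2.6, α 0.05 (two-sided assumed, since sidedness is not stated), power 0.80, losses 10%.

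n per arm = 2 × (1.960 + 0.842)² × 2.6² / 2² = 26.5, rounded up to 27. Allowing for losses, 27 / 0.9 = 30 per arm, 60 in total. The stated 60 is reproduced by a formula without a centre term.

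**2. Can the conditional rule bring centre in?** Assume blocks of 4 and 30 patients per hospital. The arms can then differ by at most 2 patients within a hospital. The worst case is 16 v 14 in one hospital and 14 v 16 in the other:

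χ² = 60 × (16 × 16 − 14 × 14)² / (30 × 30 × 30 × 30) = 0.27, p ≈ 0.61.

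A test of baseline centre imbalance would stay far from significance.

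**3. Excess width.** Let R² be the share of outcome variance due to centre. It is an assumption, because the documents give no value. With centre balanced, the true SE is the nominal SE × √(1 − R²), so the unadjusted interval is 1/√(1 − R²) times as wide as the centre-adjusted one. The true two-sided α of the unadjusted test is 2 × [1 − Φ(1.960/√(1 − R²))].

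Power for a 2-point Borg difference uses total SD 2.6 and 27 per arm, so nominal SE = 2.6 × √(2/27) = 0.708:
- unadjusted: Φ[(2 − 1.960 × 0.708) / (0.708 × √(1 − R²))]
- adjusted: Φ[2 / (0.708 × √(1 − R²)) − 1.960]

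| Assumed R² | Width ratio | True α, unadjusted | Power, unadjusted | Power, adjusted |
|---|---|---|---|---|
| 0 | 1.000 | 0.050 | 80.7% | 80.7% |
| 0.05 | 1.026 | 0.044 | 81.3% | 82.6% |
| 0.10 | 1.054 | 0.039 | 81.9% | 84.6% |
| 0.20 | 1.118 | 0.028 | 83.4% | 88.5% |

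**4. Check by simulation.** Settings: two centres split 50:50, blocks of 4 (assumed), N = 60, 10,000 runs per setting, t test against a linear model with a centre term. Centre gaps are in within-centre SDs.
- No gap: width ratio 1.00, and both methods cover at 95.1%.
- Gap 0.5 SD (R² 0.06): width ratio 1.03, coverage 95.5% unadjusted and 94.9% adjusted.
- Gap 1 SD (R² 0.20): width ratio 1.12, coverage 97.1% unadjusted and 95.2% adjusted.

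Results were similar with N = 54 and with a 70:30 split between hospitals.

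**5. What each R² means on the Borg scale.** With an even split, the gap between hospital means is 2 × √R² × 2.6. R² of 0.05, 0.10 and 0.20 needs gaps of 1.2, 1.6 and 2.3 points.

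**The case against.** **Validity is intact.** The planned test is conservative, unadjusted power stays above 80% in every row of the table, and the sample size rests on the same unstratified comparison. All of this stands. A reader might infer that the trial is biased, prone to false positives or too small, and the figures show none of these. Nor is stratification wasted, since the balance of hospitals across arms is kept whatever the analysis.

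**The loss is conditional.** A reader might conclude that the intervals are too wide as a matter of fact. They are too wide only if the hospitals differ, and the documents report no such difference. For the Borg score the top of the range needs a gap of 2.3 points, more than the 2 points that the protocol treats as clinically important, so a loss of a few percent is more plausible there.

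**No outcome is shown to lose most.** It is tempting to say that length of stay and drug use suffer most because discharge and prescribing follow local habit. The Interventions section says only that standard treatment follows medical criteria. Nothing states that practice or assessors differ between the sites, so this remains an inference.

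**The formula covers mean differences only.** It gives no size for the loss with Mann–Whitney, chi-squared or the risk ratio. This also stands.

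**This could be left to the SAP.** If the article were silent on tests, that would settle the matter. It is not silent: it names the tests and gives the one condition for adjusting, and that condition will almost never admit centre. A stated analysis that does not match the stated randomisation is a fair point on the document itself.

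**Conclusion.** The mismatch holds. Allocation is stratified by centre, and the fixed analysis is not. Its effect is a possible loss of precision. Mean-difference intervals are 2.6%, 5.4% or 11.8% too wide at an assumed R² of 0.05, 0.10 or 0.20, with nil excess at R² = 0. For the 2-point Borg difference this forgoes about 1, 3 or 5 percentage points of power. These figures rest on near balance of centre across arms, on 2.6 being the total SD, and on R² values that the documents do not supply. The point is worth acting on because the correction is nearly free, not because the planned analysis is unsafe.

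**What to change.** - **Continuous outcomes** (Borg, peak flow, length of stay, drug quantity): estimate the mean difference and its 95% interval from a linear model with treatment and centre as fixed effects.
- **Rank-test branch:** wherever Mann–Whitney would be used, specify the centre-stratified van Elteren test.
- **Dichotomous outcomes:** pre-specify a Mantel–Haenszel risk ratio stratified by centre, and state in advance the event count below which a named fallback applies. This matters for mortality. If the 12% quoted in the Background applied here (an assumption), 0.12 × 54 to 0.12 × 60 gives about 6 to 7 deaths, or roughly 3 per hospital with an even split.
- **Adjustment rule:** state that centre enters whether or not any baseline difference is significant.

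The cost is wording plus one residual degree of freedom in the linear models, out of 52 (54 patients) to 58 (60 patients). Centre is already known for every patient because the lists are centre-specific. No change to sample size or data collection is needed.

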### Blinding

Trial participants, outcome assessors and usual care providers will be blinded during the trial, and only the physiotherapists who will perform the acuTENS or sham acuTENS procedure will know the patient’s allocation. To ensure that they remain blinded to allocation, the medical staff will not be present during the application of technology. There will be no circumstances under which unblinding is permissible. Data analysis will be performed by a blinded external statistician.

### Sample size

Considering a minimal clinically important difference regarding dyspnoea, measured by the Borg scale, of 2 [16] and assuming a common standard deviation of 2.6, an α error of 0.05, a β error of 0.2 and a 10% rate of losses, we calculate that we will need to recruit 60 patients for this study. To reach this target sample size, pulmonology service and hospital emergency staff will be informed so they can detect possible candidates.

### Statistical methods

There will be a descriptive analysis of the demographic data by using means and standard deviations (mean ± standard deviation) for continuous variables and absolute values and percentages for qualitative outcomes.

For the comparative analysis between the two groups, continuous outcomes (such as Borg scale score and number of hospitalization days) will be analysed by using mean differences with a 95% confidence interval with a Student *t* test or Mann–Whitney *U* test depending on the distribution of these. For dichotomous outcomes (such as mortality at 3 months), risk ratio will also be used with a confidence interval of 95% and chi-squared test.

The main analysis will be carried out by intention to treat, but there will be another per-protocol analysis for patients who have received at least three interventions. A *P* value of less than 0.05 will be considered significantly different.

In case of missing data, last value carried forward methods will be used. In case of significant baseline differences between the two groups, there will be an adjusted analysis for these outcomes.

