Several clinical studies using AcuTENS in patients with COPD have recently been published. All studies have used the stimulation of the acupuncture point named Dingchuan (EX-B1), traditionally used to treat dyspnoea. In those studies, a decrease in dyspnoea and an increase in forced expiratory volume in 1 second (FEV 1), β-endorphin level and quality of life have been observed [11–13]. However, these studies have been conducted on patients in stable condition, and little is known about the possible effect of this technique in patients with an AECOPD. Only one case study suggesting possible benefits for shortness of breath besides an increase in the level of oxygen saturation and β-endorphins has been published to date [14], and properly designed randomized placebo-controlled trials are needed to confirm these results.

The objectives of this study are to determine whether the use of AcuTENS at the Dingchuan point (EX-B1) could be beneficial for patients hospitalized for AECOPD by reducing dyspnoea, days of hospitalization, and consumption of regular medication. Moreover, we will assess possible adverse effects of this technique and its effect on mortality and readmissions at 3 months after discharge.

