**Fig. 1 Fig1:**
[figure not shown]
Location of Dingchuan acupuncture point

The TENS simulated group (control) will have electrostimulators that are the same make and model as the experimental group but that have been modified to have no electrical outlet, even though the screen will light up and display the same data as in the unmodified device. Patients in this group will be informed that, owing to the frequency of stimulation, it is unlikely they will feel the electric stimulation.

In both groups, the session will last 45 min and will take place during a maximum of five consecutive days or until the patient is discharged.

If the acuTENS stimulation produces any kind of discomfort, the intensity of the current being applied to the patient will be reduced. If for any reason a treatment cannot be administered or is administered differently from the original protocol (e.g., only 30 min of treatment because the electrostimulation device had no battery), this will be reported. Any discomfort or skin reaction will be reported as an adverse event.

The interventions will be performed by physiotherapists or physicians who have a minimum of one year of clinical experience and who have been trained in the handling of the two treatment protocols. There will be a pre-pilot test to detect potential problems and ensure the adequacy of the implementation of the protocols.

Adherence to the treatment will be reported. No special stages for improving adherence will be taken since all patients will be hospitalized in the participating centres.

Both groups will receive the standard treatment for patients with AECOPD (bronchodilators, steroids, etc.) in accordance with medical criteria as well as the treatment with acuTENS or simulated acuTENS. No treatment is prohibited.

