### Outcomes

#### Primary outcome measure

The primary outcome of this trial will be dyspnoea using the modified Borg scale. Evaluators will show a printed Borg scale to patients and explain the meaning of each punctuation and then patients will be asked to rate their dyspnoea. Data will be assessed at baseline and after each treatment session (days 1 to 5). Differences will be assessed by comparing groups’ mean scores at each day (days 1 to 5). The modified Borg scale is a valid and reliable assessment tool for dyspnoea in patients with an AECOPD [15].

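### Carrying the last value forward past discharge can bias the later-day Borg and peak-flow differences, by an amount and in a direction the protocol does not determine

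*Protocol article*

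**What the plan says.** All references are to the protocol article.

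- **Missing data** (Statistical methods): "In case of missing data, last value carried forward methods will be used". Discharge, death, withdrawal and a missed rating are not distinguished, and no sensitivity analysis for missing values is named.
- **Length of treatment** (Interventions): the session "will take place during a maximum of five consecutive days or until the patient is discharged".
- **Rating times** (Primary outcome measure): "Data will be assessed at baseline and after each treatment session (days 1 to 5". Secondary outcome measures gives peak expiratory flow the same timing.
- **Comparison** (Primary outcome measure): "Differences will be assessed by comparing groups’ mean scores at each day (days 1 to 5". The method in Statistical methods is "mean differences with a 95% confidence interval with a Student *t* test or Mann–Whitney *U* test depending on the distribution".
- **Expected effect on stay**: the closing paragraph of Background says AcuTENS may help "by reducing dyspnoea, days of hospitalization, and consumption of regular medication". The Discussion links improved dyspnoea to fewer hospital days.
- **Blood gases** (Secondary outcome measures): taken from the clinical history where available, "since no specific analysis will be made for the trial", yet means are compared on each of days 1 to 5.

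**The concern.** No single sentence says that ratings stop at discharge. It follows from reading Interventions together with the outcome definitions: no session means no post-session rating. Part of the missing data is therefore built into the design, and by the trial's own reasoning it is related to recovery and possibly to treatment.

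Last value carried forward (LOCF) assumes that the score would not have changed after the last rating. Participants enter during an acute exacerbation with a Borg score of at least 5 and receive standard treatment, so scores can be expected to move from day to day. A patient discharged after day 3 enters the day-4 and day-5 means with a day-3 score. If the arms differ in how many patients leave early, or in how far those patients would have moved afterwards, the later-day difference is shifted.

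The rest of the section does not repair this. "there will be another per-protocol analysis for patients who have received at least three interventions" leaves out anyone discharged before a third session, which adds selection related to recovery. The 10% allowance for losses adds patients but does not remove bias.

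**Working it through.** **The plan's own figure.** Inputs from Sample size: difference 2, standard deviation 2.6, α 0.05 (taken as two-sided), power 0.80, losses 10%.

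n per arm = 2 × (1.960 + 0.842)² × 2.6² / 2² = 26.5, rounded up to 27. Then 27 / 0.9 = 30 per arm, or 60 in total. This matches the stated 60, which this point does not affect.

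**Algebra of the bias.** Let f be the share of an arm carried forward to day 5. Let g be the mean of (discharge score minus the score the patient would have had on day 5). For active minus sham, where a benefit is negative:

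bias = f_active × g_active − f_sham × g_sham

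Illustration with assumed values f_active = 0.40, f_sham = 0.20 and the same g in both arms, so that bias = 0.20 × g:

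- g = 0.5 (still improving): +0.10, towards zero
- g = 1.5 (still improving): +0.30, towards zero
- g = −1 (worsening): −0.20, away from zero

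The bias is zero only if the two products match.

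**Simulation.** The protocol gives no early-discharge rate and no post-discharge course, so these inputs are assumptions:

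- 30 per arm and 1,000 trials per scenario
- baseline mean 6.5, with mean decline 0.4 per day on sham and 0.8 on active; between-patient SD 1.0 for level and 0.42 for slope; residual SD 1.0
- scores limited to 0-10, which brings the planned day-5 difference of 2 down to about 1.8
- discharge after the day 2, 3 or 4 rating, with probability 0.3 or 0.6 once the rating is at or below 3, or 0.6 once it is at or below 4

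| Left before day 5, sham / active | Course after discharge | Would-be day-5 difference | LOCF | Relative shift |
|---|---|---|---|---|
| 9% / 22% | keeps improving | −1.81 | −1.68 | 7% understated |
| | flat | −1.60 | −1.66 | 4% overstated |
| | worsens 0.3/day | −1.58 | −1.70 | 8% overstated |
| 17% / 37% | keeps improving | −1.80 | −1.55 | 14% understated |
| | flat | −1.46 | −1.57 | 8% overstated |
| | worsens 0.3/day | −1.34 | −1.57 | 17% overstated |
| about 31% / 55% | keeps improving | −1.81 | −1.36 | 25% understated |
| | flat | −1.24 | −1.30 | 5% overstated |
| | worsens 0.3/day | −1.15 | −1.35 | 17% overstated |

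The last column is |LOCF − would-be| / |would-be|; for example 0.45 / 1.81 = 25%. The flat course still shows a small overstatement because discharge is triggered by a rating that is partly low by chance, and LOCF keeps that low rating.

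With equal slopes in both arms, the LOCF and would-be differences agreed to within about 0.01.

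**A second set of assumptions.** Here sham improved 0.5 per day, and daily discharge probability was 0.3-0.7 once Borg was at or below 3 and 0.02-0.05 otherwise. By day 5, 18-36% of sham and 30-54% of active patients had left. The complete-data difference was about 1.76 and LOCF gave 1.38-1.59, which is too small by (1.76 − 1.59)/1.76 = 10% to (1.76 − 1.38)/1.76 = 22%. Power was 72-81% against 84-86% on complete data.

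**Standard error and type I error.** Over 4,000 trials per scenario with 21-58% carried forward, the empirical and computed standard errors of the LOCF difference were 0.585/0.585, 0.589/0.582 and 0.586/0.579 with no effect. With an effect they were 0.553/0.552, 0.549/0.543 and 0.540/0.543. Rejection with no effect was 4.7-5.2%.

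**The case against.** **Little may be missing.** The protocol gives no length of stay. Its only loss figure is 10%, and it does not say whether that includes discharge. Entry requires marked dyspnoea and a recent admission, so few patients may leave before day 5, and the early days would be hardly affected. This stands. It limits the size of the problem but does not make the rule sound.

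**LOCF may be conservative.** If recovery continues, the effect is understated. That is true in those scenarios only: the direction reverses if patients worsen at home, so LOCF cannot be defended as reliably conservative.

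**The target is a choice.** Treatment is given only in hospital, so the last in-hospital score is a coherent quantity, and stay is a separate outcome. This is fair, but the protocol defines the comparison as means on each day, not as the last in-hospital score. The quantity intended after discharge has to be stated either way.

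**Stronger readings that the documents do not support:**

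- *That the standard error is wrong because imputed values count as observed.* In the largest-discharge scenario with continued improvement the day-5 SD falls from 2.29 to 1.91, about 17%, which invites this. But 2.29 is the SD of unobserved would-be scores, a different variable. Each patient contributes one independent value, and the two-sample standard error matched the real variability of the LOCF difference.
- *That values are missing mainly because of discharge.* No rate or breakdown is given.
- *That sicker patients are the ones sampled for blood gases, or that LOCF would fill most blood-gas cells.* No sampling frequency or indication is given. Recording values only where available can even be read as using observed values only.

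**Conclusion.** The concern holds as a risk of bias in the later-day differences for Borg and peak flow. It rests on a rule the protocol states, so it is not an omission that an unseen analysis plan would fill.

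The figures depend on assumed discharge rates and courses. With about 20-40% of sham and 30-60% of active patients leaving before day 5 and recovery continuing, the day-5 difference is understated by roughly 10-25%, with a loss of power. With worsening after discharge it is overstated, by 8-17% in the scenarios run. With no effect and equal discharge there is no bias, and the type I error is about 5%. The actual direction and size cannot be derived from the document.

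For blood gases the point is narrower: the general rule makes no exception for values that exist only where routine care produced them.

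This should be fixed. It does not invalidate the trial, because the evidence shows possible distortion of the estimate and loss of power, not inflated false positives.

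**What to change.** 1. Replace LOCF as the main analysis of Borg and peak flow with a mixed model for repeated measures on all observed ratings, with treatment, day, treatment × day, baseline and centre.
2. State that this model targets the score the patient would have had if still rated.
3. Add a sensitivity analysis that varies post-discharge values by arm in both directions, and keep LOCF as one of these analyses.
4. Do not carry blood gases forward. Report observed values with the number sampled per arm and day.

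**Cost.** This needs a change of wording and slightly more analysis work, with no extra patients or visits. The model assumes that data are missing at random. In the second set of simulations, where discharge depended only on the current observed score, a likelihood model on observed data gave 1.84-1.92 against 1.76, which is 5-9% too large because of the floor at 0. It is therefore not free of bias, and the sensitivity analysis is a necessary part of the change.

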### Participants

The study subjects will be patients admitted at the study centres for an AECOPD. Participants will be recruited at the time of their admission by the pulmonology service and hospital emergency staff by using the following inclusion criteria: (1) patients between 45 and 75 years of age with a diagnosis of COPD in accordance with Global Initiative for Chronic Obstructive Lung Disease (GOLD) guidelines, (2) patients with one episode of hospitalization for COPD exacerbation in the past year but not more than three episodes, (3) smoking habit history of more than 10 packs a year, (4) patients able to correctly understand and answer the modified Borg scale, (5) patients with an initial degree of dyspnoea with a score of at least 5 in the modified Borg scale at recruitment, (6) patients recruited for the study during the first 48 h of hospitalization, and (7) patients who agree to participate in the study and sign the informed consent form.

Exclusion criteria will be (1) patients with any contraindication for transcutaneous electrical stimulation (patients with pacemakers, skin injury in the application area, etc.) and (2) patients with any cardiovascular, neurological or psychiatric disease that may affect the perception of dyspnoea.

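### Baseline Borg enters the analysis only if a baseline significance test is positive, so the planned comparison is valid but loses power, and neither the adjusted result's status nor the test is fixed

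*Protocol article*

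**What the plan says.** All references are to the protocol article.

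- **Primary outcome measure.** On collection of the Borg score: "Data will be assessed at baseline and after each treatment session (days 1 to 5"). On its comparison: "Differences will be assessed by comparing groups’ mean scores at each day (days 1 to 5"). No baseline term appears.
- **Statistical methods, choice of test.** Continuous outcomes are reported as mean differences with 95% confidence intervals, using a Student t or a Mann–Whitney U test, "depending on the distribution of these". No criterion for the choice is given.
- **Statistical methods, adjustment.** "In case of significant baseline differences between the two groups, there will be an adjusted analysis for these outcomes". The covariates, the model and the status of the adjusted result are not stated.
- **Sample size.** The target is set by "Considering a minimal clinically important difference regarding dyspnoea, measured by the Borg scale, of 2" and by "assuming a common standard deviation of 2.6". This is a raw SD with no allowance for baseline.
- **Participants.** Entry is limited to "patients with an initial degree of dyspnoea with a score of at least 5 in the modified Borg scale at recruitment".

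**The concern.** In a randomised trial a significant baseline difference arises by chance, so a baseline test is a poor guide to whether adjustment is worthwhile. What matters is how strongly the baseline score predicts the outcome. The rule therefore leaves out a measured and probably predictive covariate in nearly every realisation of the trial, and a baseline gap that falls short of significance can still move the estimate.

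Two further points are left loose. If the baseline test is positive there will be two Borg results, and the text does not say which is the main one. If the rank test is selected, the test no longer matches the mean difference and interval that the plan promises. At stake are precision on the primary outcome of a 60-patient trial and a single, identifiable primary result.

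**Working it through.** **Inputs.** Difference 2, SD 2.6, α 0.05, β 0.2, losses 10% (Sample size); 1:1 allocation (Trial design). The sidedness of α is not stated, but two-sided reproduces the plan's figure. The correlation r between baseline and post-treatment Borg is not in the documents; 0.3, 0.5 and 0.6 are assumed.

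**1. The plan's own figure.** n per arm = 2 × (1.960 + 0.842)² × 2.6² / 2² = 26.5, so 27 per arm and 54 in total. 54 / 0.9 = 60, as stated.

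**2. How often the rule fires.** Under randomisation a baseline test at 0.05 is positive in about 5% of trials per variable, so baseline Borg stays out of the analysis in about 95%.

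**3. What a non-significant gap can do.** With 27 per arm, the largest baseline gap that is still non-significant is 2.007 × √(2/27) = 0.546 baseline SDs. It shifts the unadjusted estimate by up to r × 2.6 × 0.546:

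- r = 0.3: 0.43 points
- r = 0.5: 0.71 points
- r = 0.6: 0.85 points

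That is 21% to 43% of the 2-point target. These are upper limits at the edge of significance, not typical values, and the shift can go either way.

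**4. Power for one day's comparison.** The unadjusted standard error is 2.6 × √(2/27) = 0.708. ANCOVA has residual SD 2.6 × √(1 − r²), so its standard error is smaller by the factor √(1 − r²), that is by 5%, 13% or 20%. Noncentral-t power is 79.2% unadjusted. In the simulation (27 per arm, normal data, 40,000 runs per r), the planned rule was read as using ANCOVA when the baseline t test is significant and the raw t test otherwise.

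| r | Residual SD | ANCOVA power, noncentral t | Simulated: raw t | Simulated: planned rule | Simulated: ANCOVA always |
|---|---|---|---|---|---|
| 0.3 | 2.48 | 82.8% | 79.2% | 79.4% | 82.0% |
| 0.5 | 2.25 | 89.3% | 79.0% | 79.9% | 88.9% |
| 0.6 | 2.08 | 93.4% | 79.0% | 80.4% | 92.8% |

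The simulated ANCOVA figures are slightly lower because they include the small cost of chance baseline imbalance. At r = 0.5 the planned rule recovers 79.9 − 79.0 = 0.9 points of an available 88.9 − 79.0 = 9.9.

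**5. Type I error** (100,000 null runs per r). The planned rule gives 4.7%, 4.2% and 4.0% at r = 0.3, 0.5 and 0.6; ANCOVA gives 4.9% to 5.0%.

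**6. t or Mann–Whitney.** The protocol gives no criterion, so a Shapiro–Wilk test was assumed (8,000 runs). Type I error was 5.1% with normal data and 4.6% with rounded, bounded, Borg-like data. If the smaller of the two p-values were always taken, it was 6.0% and 5.1%.

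**The case against.** The strongest reply is that nothing promised is lost. The trial was sized on the raw SD, the unadjusted comparison has about its planned 80% power, it is unbiased under randomisation, and its confidence interval already allows for chance imbalance. All of that stands. So does the caution about size: r is unknown, and a minimum Borg of 5 at entry narrows the baseline range and may lower it. At r = 0.3 the simulated gain over the planned rule is 82.0 − 79.4 = 2.6 points.

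Stronger readings are tempting, but the documents do not support them:

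- *The data choose the headline result.* A reader might infer that the adjusted result displaces the unadjusted one. The text says only that an adjusted analysis will be done; a supplement to a fixed unadjusted comparison is an equally natural reading. The fault is that the status is unstated.
- *The rules inflate false positives.* The adjustment rule is at or below the nominal level, and a Shapiro–Wilk gate stays near it. Only free choice of the smaller p-value went above 5%, and the external statistician is to be blinded (Blinding).
- *The rule would fire often across many baseline variables.* No list of variables to be tested is given. Borg and peak flow are the outcomes with a stated baseline measurement; for two independent variables the chance is 1 − 0.95² = 9.75%.
- *Different tests on different days.* This is possible, but the text does not describe selection day by day.

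It can also be said that a separate analysis plan would settle the details. The criterion for the test and the form of the adjusted model could indeed be left to it. The significance trigger is different: it is a stated rule, which such a plan would have to override.

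**Conclusion.** The point holds as one of efficiency and clarity, not validity. The stated rule leaves baseline Borg unused in about 95% of trials and recovers almost none of the available gain. With 27 evaluable per arm, a difference of 2 and an SD of 2.6, power is about 79% unadjusted against about 83%, 89% or 93% with ANCOVA at r = 0.3, 0.5 or 0.6. Those gains rest wholly on the assumed correlation, and the lowest may be the most realistic. Independently of r, the protocol should say which Borg result is primary and should tie the test to the mean difference it reports. The change is worth making because it costs nothing in patients or measurements.

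**What to change.** Before unblinding:

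1. Delete the rule that makes adjustment depend on a baseline significance test.
2. Pre-specify one primary linear model for Borg: ANCOVA with treatment group and baseline Borg, whatever the baseline comparison shows, and the same model on every day.
3. Name the adjusted mean difference with its 95% confidence interval as the primary result.
4. Treat peak expiratory flow the same way, with its own baseline.
5. Keep Mann–Whitney as a sensitivity analysis only, not as an alternative selected from the distribution.

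The cost is a change of wording in the protocol or analysis plan. Both baselines are already collected, and the target of 60 need not change.
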